## Background

Cognitive deficits are seen in 50 to 80 % of those dependent on alcohol [1] currently there is no effective treatment. The cognitive functions particularly affected in alcohol dependence are learning new skills, visuospatial ability, executive function (planning, capacity for abstraction and effortful processing), and aspects of attention, whilst verbal skills usually remain intact [2–6]. The cognitive deficits not only affect the quality of life of those dependent on alcohol and the amount of health care they need, but also have a detrimental effect on ability to benefit from treatment programmes [4, 7, 8]. Depression is a major symptom in many people who are dependent on alcohol, and is associated with greater tendency to relapse drinking [9]. Most depressive symptoms in this population are secondary to the alcohol dependence and gradually resolve spontaneously. Despite this, improvement in symptomatology could provide faster and more complete recovery and would aid abstinence.

The majority of those dependent on alcohol undergo frequent episodes of withdrawal and resumption of drinking, and clinical evidence indicates that “kindling” occurs, as a higher number of withdrawal episodes are associated with greater severity of withdrawal, including greater memory impairment [10]. Schandler et al. [11] found visuospatial learning was worse in those dependent on alcohol during abstinence than in those who were still intoxicated. People who experienced more alcohol withdrawal episodes have been found to have greater subsequent memory deficits [12]. Preclinical data also demonstrated that withdrawal is an important factor in causing the memory deficits. Memory and learning deficits were found in rats in a variety of tests after alcohol withdrawal, but not during alcohol intake [13, 14]. These data suggest that the neurotoxicity that is known to occur during acute alcohol withdrawal may play a contributory role in the subsequent cognitive deficits so frequent in those who are dependent on alcohol [15].

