### Study entry

Prospective participants who are referred for an admission to an alcohol inpatient unit for alcohol detoxification will be identified by the community alcohol teams. If the person is willing to hear more about the research, contact details will be passed to the research team. Written informed consent to complete a preliminary screening appointment will be taken. Eligibility to take part in the research will be checked at a preliminary screening appointment and included administration of the Mini-Mental Sate Examination (MMSE) [39] to screen for any severe cognitive impairment. The Composite International Diagnostic Interview (CIDI) [40] will be administered to demonstrate alcohol dependence of at least 5 years of the patients prior to detoxification according to DSM-IV diagnostic criteria. Plasma alanine aminotransferase (ALT) and creatinine will be measured for indication of liver damage and impaired renal function, respectively. Urine will be tested for evidence of porphyria. If the participant is eligible, consent to take part in the study will be obtained prior to or on admission to the alcohol unit by a clinical member of the research team or a delegated physician. All participants will be advised not to consume grapefruit juice during the trial as this is contraindicated with mifepristone.

At the preliminary screening appointment participants will be asked to complete questionnaires to help establish patterns of alcohol consumption. This includes a measure of the severity of alcohol dependence using the Severity of Alcohol Dependence Questionnaire (SADQ) [41], current craving for alcohol using the Alcohol Urge Questionnaire (AUQ) [42], problems experienced due to alcohol using the Alcohol Problems Questionnaire (APQ) [43], and a retrospective report of the quantity of alcohol consume over the previous 90 days collected using the time-line follow-back (TLFB) [44]. In addition, the Fagerstrom questionnaire [45] will be used to record the amount of smoking and level of nicotine dependence and symptoms of depression will be measured using the Beck Depression Inventory (BDI-II) [46].

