### Primary outcome measures

Cognitive ability will be measured using the CANTAB. The CANTAB has been used extensively in research and previous studies have been published that have used the CANTAB test battery in patients with depression and patients with alcohol dependence [47–52]. The CANTAB testing will compare mifepristone and placebo groups concurrently. Cognitive function measurement prior to mifepristone/placebo would not be valid owing to intoxication. A pretest will be carried out on the day before the first CANTAB testing, composed of the Motor Screening task and the Reaction time task. These two tests are designed to assess basic motor and visual skills and determine whether participants are capable of being tested on CANTAB. The CANTAB tests that will be used at the two cognition testing times (between days 13 and 20 and 21 and 28) are: visuospatial ability by Reaction Time, Pattern Recognition, Matching to Sample Visual Search, Spatial Recognition memory and Paired Associates tasks; sustained attention by the Rapid Visual Processing task; and executive function by Intra- and Extra-Dimensional Shifting, Spatial Working Memory and Stockings of Cambridge tasks.

The above CANTAB test times will enable examination of cognitive testing administration of chlordiazepoxide ceases, as benzodiazepines are well established to affect memory and learning. Urine samples taken on the day of CANTAB testing will be screened for the presence of residual chlordiazepoxide or its active metabolites, which may affect cognitive performance [53].

The BDI-II [46] will be used to record symptoms of depression throughout the trial. It will be administered at every 7 days during the 4 weeks the participant is in the trial and at 3, 6 and 12 months follow-up from cessation of drinking. The BDI-II will be administered on the day of the CANTAB testing so that the results can be used as a variable in the measure of cognitive function.

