### Statistical analysis

The null hypothesis is that there will be no differences in the results from the cognitive testing between participants who received mifepristone and those who received the placebo. Primary data analysis will be by analysis of variance (ANOVA) on the CANTAB results and Beck depression scale scores for mifepristone and placebo groups, with post hoc tests for variables likely to affect these results. Analysis will be carried out both on a per protocol basis and an intention to treat basis.

A repeated measures analysis of variance using treatment type as a between-subject factor (two levels: mifepristone and placebo) and number of times the scale is applied as the within-subjects factor (five levels) will be carried out on the Beck depression scale results. This analysis will examine changes in level of depressive symptoms over the 4 weeks of the study. The analysis on the results from the BDI-II will compare the depressive symptoms prior to mifepristone/placebo with the scores during the four test weeks. This will provide information about whether or not mifepristone alters the progression of such symptoms and enable effect sizes to be calculated for such multiple comparisons in a full trial.

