#### Post hoc analysis

Although participants in the two treatment groups will be balanced, potential confounds will be examined as covariates in the post hoc ANCOVA analysis. Covariates will include: severity of withdrawal symptoms (measured by the CIWA-Ar, which primarily examines autonomic symptoms, and the AUQ which measures alcohol craving); presence/absence of depressive symptoms; smoking/non-smoking, chlordiazepoxide dosage; other medication prescribed after detoxification; co-morbid psychiatric disorders other than depression, other medication and age.

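### The post hoc ANCOVA of the CANTAB outcomes codes depression and smoking as yes/no although graded scores are collected before randomisation; the loss of precision is real but modest

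*Protocol article*

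**What the plan says.** The Statistical analysis section of the protocol article sets the main comparison: "Primary data analysis will be by analysis of variance (ANOVA) on the CANTAB results and Beck depression scale scores". Adjustment comes afterwards. The Post hoc analysis section says that "potential confounds will be examined as covariates in the post hoc ANCOVA analysis" and names among them "presence/absence of depressive symptoms; smoking/non-smoking, chlordiazepoxide dosage". Other covariates in the same list are graded: withdrawal and craving by CIWA-Ar and AUQ, benzodiazepine by dosage, and age.

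Graded forms of the two yes/no items exist before randomisation. In the Study entry section, "the Fagerstrom questionnaire [45] will be used to record the amount of smoking and level of nicotine dependence", and the BDI-II is completed at the same screening appointment.

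Two further statements bear on depression. The Primary outcome measures section has the BDI-II given again on the days of CANTAB testing, "so that the results can be used as a variable in the measure of cognitive function", without saying how it will be coded. For depression as an outcome, the Statistical analysis section says that the BDI-II analysis "will compare the depressive symptoms prior to mifepristone/placebo with the scores during the four test weeks".

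**The concern.** Cutting a graded score into two groups treats everyone on the same side of the cut as alike. The covariate then removes less outcome variance, and imbalance between arms in the degree of depression or nicotine dependence within a category stays uncorrected.

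This matters more than usual for CANTAB. The Primary outcome measures section explains that testing before treatment would not be valid because of intoxication, so there is no cognitive baseline to adjust for. Minimisation covers dependence severity, site and age, but not depression or smoking. Other pre-randomisation measures are therefore what the adjusted cognitive comparison has to work with.

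Timing is a second issue. The Post hoc analysis section does not say which BDI-II administration defines the yes/no depression term. A test-day value is measured after treatment and is itself a primary outcome, so adjusting the cognitive result for it could take out part of any treatment effect.

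**Working it through.** **1. The plan's own figures.** The article gives no figure for the loss from yes/no coding. Its sample size supplies the scale for judging consequences. With two-sided alpha 0.05 and 80% power, n per group = 2(1.960 + 0.842)²/d²:

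- d = 0.8: 24.5, so 25 (stated 25)
- d = 0.7: 32.04, so 33 (stated 32, a rounding difference)
- d = 0.5: 62.8, so 63 (stated 63)

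The stated total of 120 is 60 per arm if allocation is equal. Power for d = 0.5 without a covariate is then Φ(0.5·√(60/2) − 1.960) = Φ(0.779) = 78.2%.

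**2. Loss from a split, normal score.** If the score is normal and the outcome is linear in it, a split with proportion p on one side retains φ(z_p)²/[p(1−p)] of the explained variance.

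| Split | Retained | Lost |
|---|---|---|
| 50/50 | 0.1592/0.25 = 0.637 | 36% |
| 70/30 | 0.576 | 42% |
| 80/20 | 0.0784/0.16 = 0.490 | 51% |
| 90/10 | 0.0308/0.09 = 0.342 | 66% |

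**3. Other shapes (assumed).** Over splits from 50/50 to 90/10, a uniform score loses 25% to 73%. An exponential score loses 35% to 90%, depending on the share above the cut.

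For smoking, a score with non-smokers at zero is more plausible than a normal one. If a share p smoke and smokers have mean m and SD s, the loss is s²/[s² + (1−p)m²]. With s = 2.3:

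- p = 0.5, m = 6: 5.29/(5.29 + 18) = 23%
- p = 0.9, m = 4: 5.29/(5.29 + 1.6) = 77%

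Simulation with scores rounded and limited to 0–10 gives 22% and 75% for these two cases, the extremes over 50% to 90% smokers and means of 4 to 6.

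**4. Consequence for power.** A covariate explaining R² of outcome variance reduces the residual SD to √(1−R²); the split reduces it only to √(1−R²(1−loss)). At 60 per arm and d = 0.5, with R² assumed and losses of 36% to 66%:

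| R² of graded score | Power, graded | Power, yes/no | Difference (points) |
|---|---|---|---|
| 0.05 | 80.2% | 79.5% to 78.9% | 0.7 to 1.3 |
| 0.10 | 82.3% | 80.8% to 79.6% | 1.5 to 2.7 |
| 0.20 | 86.5% | 83.5% to 81.0% | 3.0 to 5.5 |

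For R² = 0.10 the residual SD is √0.900 = 0.949 graded, against √0.936 = 0.967 to √0.966 = 0.983 with the split. The graded version is therefore about 2% to 3.5% smaller.

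**The case against.** The strongest reply is that this is a secondary detail of a proof-of-concept trial. The adjusted analysis is post hoc, and the primary ANOVA does not use these covariates. The Trial status section reports 26 + 1 = 27 participants. At about 13 per arm an unadjusted t-test has only some 23% power for d = 0.5, so a 2% to 3.5% change in residual SD alters little. This stands, and it limits the weight of the point.

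The depression half is also partly covered. The pre-treatment BDI-II already enters the repeated-measures analysis of depression, and the test-day BDI-II is meant to serve as a variable for cognition. The first of these confines the point to CANTAB. The second does not answer it, because the covariate list names the yes/no form and a test-day score is post-treatment.

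The smoking half is weaker. Setting non-smokers to zero on the Fagerstrom assumes that being a smoker and the degree of dependence lie on one linear scale. If the effect is mainly one of smoking status, the yes/no term may do as well or better.

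Three stronger readings are tempting but unsupported:

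- That the plan is known to discard a third to two thirds of the usable variance. This range holds only for a normal score, a linear effect and splits from 50/50 to 90/10, none of which the article supplies.
- That the depression split must be lopsided. The Background section says "Depression is a major symptom in many people who are dependent on alcohol". That gives no proportion, so neither the upper half of the range nor a claim that most participants fall in one category follows.
- That the missing BDI-II cut-off leaves the split open to choice after the data are seen. An article may leave the cut-off to the full protocol or analysis plan, so its absence is no finding.

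**Conclusion.** The point holds in limited form. The article states a yes/no coding for two covariates whose graded versions it collects before randomisation, and for the post hoc CANTAB ANCOVA that coding gives up precision. Under normality and linearity the loss of explained variance is 36% at an even split, rising to 66% at 90/10. For a zero-inflated Fagerstrom score it is roughly 22% to 75%. In power terms this is about 1 to 3 points at 60 per arm if the covariate explains 5% to 10% of outcome variance, and about 3 to 5.5 points at 20%. These R² values, the splits and the score shapes are all assumptions.

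The depression half is the firmer one, because the screening score also settles the timing problem. The smoking half depends on the form of the relation with cognition. The primary analysis is unaffected, and this is a refinement rather than a defect that threatens the trial's conclusions.

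**What to change.** In the post hoc ANCOVA of the CANTAB outcomes:

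- Replace the yes/no depression covariate with the continuous BDI-II score from the screening appointment, and say that it is the screening score. Coding and timing are then both fixed, and no post-treatment value is adjusted for.
- Where smoking is adjusted for, use the graded Fagerstrom score, either alone with non-smokers at zero or alongside smoking status if a single linear scale is doubted.
- If the yes/no coding is kept for either, give the reason.

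Do not carry the screening BDI-II into the repeated-measures BDI-II analysis as a covariate. The pre-treatment score is already one of the responses there, and it would appear on both sides of the model.

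Cost: no new data are needed. The depression change leaves the number of model terms as it is. The smoking change adds one term only if status and score are both used, which is worth weighing with 27 participants. The choice should be recorded before the data are locked for analysis.

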### Data management

Data will be anonymised and be stored by secure means. Electronic data will be stored on password protected computers or laptops. Hard copy data will be stored in locked filing cabinets in lockable offices in buildings with swipe access and security presence. All data will be entered into a computerised data entry system at King’s College London. At the end of the study arrangements will be made with the appropriate data repository service for transfer and preservation of the data in accordance with the principles agreed by the NHS and the MRC for the preservation and sharing of clinical data.

The results from the CANTAB cognition testing have to be entered directly on to a laptop as this is an integral part of this testing. Immediately at the end of each test session, the data entered on the laptop will be encrypted using a file encryption key to which only the research team will have access. No personal data will be entered on the laptop; the data will be stored under code numbers so that individual participants cannot be identified. As soon as possible after the end of a test session the data will be transferred to a secure server at King’s College London and the data erased from the laptop.

In order that contact can be made for the follow-up interviews, identifiable patient information will be accessed by the research team from the medical notes, with the patient’s consent. No personal information will be stored with the trial data.

Arrangements will be made for a copy of all the original data to be “locked” electronically prior to the analysis and kept at King’s College London in a secure location so that a record will be available of all the original results. The data will also be stored on the computer data system for archiving at the end of the study.

The investigators and Institution will permit trial-related monitoring, audits, Research Ethics Committee and Research and Development department review and regulatory inspections by providing direct access to source data and other documents (results of cognitive testing, depression scales, blood, saliva and urine test reports) and data analysis results.

### Monitoring

An independent Steering Committee has been set up, chaired by [name], Newcastle University. Members: [name] [name], Imperial College and [name], Sussex University. The Medical Research Council has approved this membership. A Data Monitoring Committee has been set up and includes a statistician who is not otherwise involved in the project. A project management group will meet regularly to monitor the progress of the trial. This group will include the Chief Investigator, the Principal Co-Investigators, the researchers and clinicians and user representative. The trial will also be monitored in accordance with the King’s Health Partners Clinical Trials Office Quality Policy.

## Discussion

Preclinical trials have suggested that Type II glucocorticoid receptor activation during acute alcohol withdrawal is related to impairment of cognitive function. Treatment with mifepristone, a Type II glucocorticoid receptor antagonist, may protect against this. Clinical studies have shown that mifepristone has a beneficial effect in depression. The MIFCOG study is the first clinical trial to examine the role of glucocorticoid receptor activation in cognitive function and depression during protracted alcohol withdrawal, and the efficacy of treatment with mifepristone.

### Trial status

Recruitment for the trial began in September 2012 and was completed in May 2015. A total of 26 participants were recruited between September 2012 and September 2014. The trial experienced several challenges in recruitment over this 2 year period including retendering of NHS addiction services and the closure of NHS specialist addiction units at participating research sites. In September 2014 the decision was made to recruit participants who were completing their detoxification as an outpatients as well as an inpatients, to increase the number of potential participants. This decision was made following advice from the Trial Steering Committee and the Data Monitoring Committee and the results of the safety report following recruitment of the first 20 participants. Approval from the MHRA and local Research Ethics Committee to recruit participants completing their detoxification as outpatients was granted in November 2014. The study protocol was largely unchanged for outpatient recruitment, with the following exceptions;Saliva sample collection was removed as it was not possible to gain reliable waking samples if participants were not an inpatient.CIWA assessments were only completed for days 2–5 as there were insufficient staffing resources to complete these assessments at a weekend.Plasma samples taken on days 7 and 14 were taken on days 7 and 14 +/− 2 days to allow for times when they fell on a weekend.

Following approval to recruit participants completing their detoxification as outpatients as well as those completing a detox as inpatients only 1 further participant was recruited. Completion of the final 12 month follow-up will be completed in May 2016.
